# Effect of an artificial intelligence-assisted tool on non-valvular atrial fibrillation anticoagulation management in primary care: protocol for a cluster randomized controlled trial

**DOI:** 10.1186/s13063-022-06250-8

**Published:** 2022-04-15

**Keywords:** Atrial fibrillation, Artificial intelligence, Clinical decision support system, Community health center, Guideline adherence, Cluster randomized controlled trial, Protocol

## Abstract

**Background:**

Atrial fibrillation (AF) is one of the most common cardiac arrhythmia diseases. Thromboembolic prophylaxis plays an essential role in AF therapy, but at present, general practitioners (GPs) are presumed to lack the knowledge and enthusiasm for AF management. Clinical decision support systems (CDSS), assisted by artificial intelligence, help primary care providers (PCPs) make quick, individualized, and correct clinical decisions. This primary aim of the study is to identify whether the promotion of the CDSS would improve the primary care provided to patients with AF. The secondary objectives are mainly to assess the health-economic and clinical benefits from using the CDSS, and the improvement of GPs’ AF management capability.

**Methods:**

This study will be a prospective cluster randomized controlled trial, conducted among 14 community health centers in Shanghai which were randomized as the intervention group and control group in a ratio of 1:1. The intervention group will use the CDSS in the consultation of patients with AF and the control group will maintain their usual care. The trial will include 498 patients with AF and the follow-up period will be 12 months. The primary outcome is set as the proportion of antithrombotic treatment prescriptions in agreement with recommendations in the latest China’s AF-related guidelines. The secondary outcomes are the frequency of consultation, the compliance rate of international normalized ratio (INR) in patients with warfarin, stroke morbidity, treatment compliance, medication satisfaction, and the cost-benefit analysis. Per-protocol (PP) analysis and the intention-to-treat (ITT) analysis will be conducted.

**Discussion:**

This study aims to identify whether the application of CDSS to manage patients with AF in China’s community health centers would bring benefits for patients, physicians, and health economics.

**Trial registration:**

Registry name: 非瓣膜性房颤社区AI辅助管理工具研发及推广效果研究 (Development and promotion of an AI-assisted tool for NVAF management in primary care); registry number: ChiCTR2100052307; registration date: Nov. 22^nd^, 2021; http://www.chictr.org.cn/showproj.aspx?proj=133849.

**Supplementary Information:**

The online version contains supplementary material available at 10.1186/s13063-022-06250-8.

## Background

### Introduction

Atrial fibrillation (AF) is one of the most common cardiac arrhythmia diseases [1], with more than 7.90 million patients with AF in China over 45 years of age, with a prevalence of 1.8% for general population and 3% for people over 75 years in 2020. In a rapidly aging population, it was estimated that the prevalence of AF would increase at least 2.5 times in the next 50 years [2] and the health risk to patients and the disease costs for the country would only increase as AF caused a twofold increase in all-cause mortality in women and a 1.5-fold increase in men [3]. Thromboembolic events, especially ischemic stroke, are the main issue [4], with the risk of ischemic stroke in patients with AF was four to five times higher than that in those without, and 70% of patients with a stroke caused by AF had poor outcomes [5]. Thromboembolic prophylaxis plays an essential role in AF management, with many studies indicating that both new oral anticoagulants (NOACs) and warfarin reduced all-cause mortality and the incidence of stroke and thromboembolic events among Asian and non-Asian patients [6]. However in 2013, the China Registry of Atrial Fibrillation (CRAF) study reported that among patients with AF in China with a high stroke risk where the CHA_2_DS_2_-VASc score exceeded two, only one in five received antithrombotic treatment, nearly 2/3 of patients received antiplatelet drugs, and almost one in 10 patients had no treatment at all [7]. The compliance rate of international normalized ratio (INR) in patients with warfarin was only 31.8%, based on patients with AF treated with warfarin whose time within therapeutic range (TTR) exceeded 60%.

Some scholars highlighted the view of “integrated care and stratified therapy,” which meant that patients could get access to comprehensive management in primary care, such as risk assessment, AF treatment, INR monitoring, health education, and treatment of comorbidity diseases, with upper hospitals responsible for the treatment of complications, emergencies, and operations [8]. China’s guidelines also suggested a comprehensive geriatric assessment (CGA) for old patients with AF, including fall risk, cognition, emotion, and psychology [9]. It is possible to move AF management work into community health centers, because of the progress China had made in primary care, the implementation of a two-way referral system [10], and the improvement in general practitioners’ (GPs’) work competence.

In daily practice, the process is not always followed, as GPs are busy at their work and they do not always get access to the latest guidelines promptly. Many GPs avoid AF management and some know little about the disease and antithrombotic therapies, so at present in China’s community health centers, AF is usually ignored by GPs, resulting in many patients seeking healthcare in superior hospitals or remaining in an unmanaged state [11].

Artificial intelligence (AI) collects massive amounts of medical data and knowledge, with technical advantages such as precise clustering and reinforcement learning and it can be advantageous to GPs by making data more accessible and freeing them from complex calculations [12]. Clinical decision support systems (CDSS), supported by computer algorithms, help primary care providers (PCPs) quickly make individualized and correct clinical decisions by combining patients’ data with guidelines and using evaluation tools in a short consultation [13]. The CDSS process can significantly improve GPs’ work efficiency and quality and reduce their workloads, making it a promising development in China’s primary care [14]. At present, CDSS are used mainly in the management of oncology and cardiovascular diseases [15–17], and AF antithrombotic management-associated CDSS are also be used in practice. Researches into the effect of CDSS on the management of AF have occurred in many developed countries, but due to the short follow-up time, inadequate sample sizes, and the imperfect design of their CDSS, many studies reported that CDSS improved the appropriate prescription of antithrombotic agents, and lowered the incidence of adverse events, but had no effect on the incidence of thromboembolism [18–23]. Unlike developed countries, the healthcare in developing countries is poor with a lower proportion of appropriate antithrombotic treatment in patients with AF [24] and initial consultation in primary care is not fully implemented. Therefore, it is necessary to study the effect of CDSS again in developing countries [25], exploring if any improvement would be obtained by applying AF management CDSS in these regions.

We cooperated with Ping An Healthcare and Technology Co., Ltd., referring to China’s latest AF guidelines, expert censuses, and suggestions, and combing some assessments of CGA [9], to develop an AI-assisted AF-related CDSS for GPs by integrating fusion data and knowledge modeling technology. In the previous pilot study, we applied the CDSS in one community health center as the software group, managing 53 patients for over 1 year and had a significantly increased proportion of appropriate anticoagulation compared with the control group which performed usual care. However, the pilot study included only two community health centers and a few patients. In this study, the CDSS was updated and optimized to solve the shortcomings discovered in the previous trial and more subjects will be enrolled from more community health centers.

### Objectives

The primary objective of this study is to identify whether the promotion of the CDSS would improve the primary care provided to patients with AF. The secondary objectives are mainly to assess the health-economic and clinical benefits from using the CDSS, and the improvement of GPs’ AF management capability. By promoting the CDSS, we hope to accelerate the process of prioritizing AF management in community health centers and the implementation of the two-way referral system.

## Methods

### Study design

This study is a prospective, paralleled, open-label, single-center cluster randomized controlled trial. The Ethics Committee of Zhongshan Hospital approved the present study protocol (Approval Number: B2021-579(2)). The study was registered in the Chinese Clinical Trial Registry, International clinical trials registry platform of the World Health Organization (Registration Number: ChiCTR2100052307). This protocol was designed and described according to the standard protocol item- Recommendations for Interventional Trials–Artificial Intelligence (SPIRIT-AI) extension published in 2019 [26] (Additional file 1) and the consolidated standards of reporting trials (CONSORT) 2010 statement: extension to cluster randomized trials [27].

### Patients and public involvement

Neither patients nor the public were or will be involved in the design, planning, conduct, or reporting of this study.

### Settings and participants

The requirements for using the CDSS in community health centers are that their servers of the hospital information systems (HISs) are at least with eight-core central processing unit, 32 GB RAM, hard drive of 500 G, and operating system of Centos 7.2. Fourteen community health centers willing to participant in this study in Baoshan District and Jing’an District of Shanghai were recruited by researchers. Baoshan District and Jing’an District are in the suburb and urban area of Shanghai, respectively, so are geographically representative (Additional file 2).

The participants are GPs and patients with AF in the selected community health centers. For GPs, the inclusion criteria are that they work in GP consulting rooms or the AF special consulting rooms in their community health center, are willing to participate in the study, and can complete the pre-training on AF management and CDSS use. They will be excluded if they rarely use computers in their daily work, or cannot complete the whole study.

Patients will be included if they are 18 years old or older, diagnosed with any type of AF or atrial flutter (ICD-10 codes shown in Additional file 3) during a consultation or in medical history, registered with GP for at least 1 year, and are willing to participate in the study and sign the informed consent (Additional file 4). They will be excluded if they are diagnosed with end-stage disease such as advanced tumors, or their expected survival time is less than 1 year, or are unable to cooperate with the study due to illiteracy or dementia, or cannot continually consult in the registered community health centers in the next 1 year due to objective conditions such as moving, or with valvular AF or prosthetic valves, or are participating in other clinical trials related to AF, or are pregnant or breastfeeding. Subjects can reserve the right to drop out due to any reason or without reason and at any time during the study. If any incident happens to the subjects, such as death, disability, or dementia, they could withdraw from the study after applying by their legal representatives and evaluating by researchers. Subjects who are pregnant during the follow-up and plan to give birth will be considered as withdrawal.

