### Randomization and blinding

#### Sequence generation

Stratified randomization was conducted considering the location of each community health center.

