#### Allocation concealment mechanism

The allocation results of each community health center were told to the administrators by telephone. Each administrator only knows the result of his or her own site.

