#### Preparation

Prior to be used, the CDSS will be embedded into the HIS of community health centers in the intervention group. The GPs will be trained in the use of the CDSS within the intervention group by developers from Ping An Healthcare and Technology Co.Ltd., and GPs of both groups will be trained in AF management by the researchers. After training, the training materials will be bound into a handbook and provided to the GPs for free.

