### Enrollment and follow-up

GPs will be first enrolled, trained, and invited to complete the same KAP questionnaire on antithrombotic treatment three times before and after the training and at the end of the study. In the last month, one GP in each community health center of the intervention group will be randomly selected for a semi-structured interview. After training, GPs can enroll patients with AF that meet all the inclusion criteria and none of the exclusion criteria into this study, after signing the informed content. The follow-up will last for 12 months. Within the first week and the fourth, eighth, and twelfth months after enrolling, patients will be required to finish the PSQ-18 questionnaires. Patients will be contacted by telephone at the last week of a month or the first week of the next month, if they do not revisit their doctors in that month. One free INR point-of-care testing (POCT) collecting finger-stick blood will be provided to patients who complete all the 1 year time’s follow-up and the reasons for patients not finishing the study will be collected if possible. The study flowchart is shown in Fig. 4.

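### The GP inclusion rule names CDSS training for both arms, but only intervention GPs are given it, so the criterion can screen GPs in one arm only

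*Protocol article*

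**What the plan says.** Settings and participants gives one set of GP criteria with no distinction by arm. GPs must work in a GP or AF consulting room, be willing to take part, and they qualify if they "can complete the pre-training on AF management and CDSS use". The exclusion sentence, also common to both arms, reads: "They will be excluded if they rarely use computers in their daily work, or cannot complete the whole study".

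Preparation splits the training: "The GPs will be trained in the use of the CDSS within the intervention group by developers", whereas "GPs of both groups will be trained in AF management by the researchers".

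On timing, Sequence generation says "Stratified randomization was conducted considering the location of each community health center", and Allocation concealment mechanism says "The allocation results of each community health center were told to the administrators by telephone". Both are in the past tense. Enrollment and follow-up looks ahead: "GPs will be first enrolled, trained, and invited to complete the same KAP questionnaire on antithrombotic treatment three times". Trial status plans participant enrolment for January 2022. The Blinding section leaves researchers, participants and analysts unblinded.

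The enrolled GPs supply the data in three ways. Their anticoagulation decisions are the primary outcome, their KAP scores are a secondary outcome, and after training they enrol the patients.

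**The concern.** Cluster randomisation makes the centres comparable. It does not protect the comparison of GPs chosen within centres afterwards if the choice depends on the arm. A criterion that mentions CDSS training can be put to the test where that training is held. In control centres it is never held, so the criterion either lapses or rests on a guess. Nothing in the article says how it applies there, or that GPs were listed before allocation was known.

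If GPs who struggle with or decline the software session are left out in intervention centres, while similar GPs stay in at control centres, part of any difference in guideline agreement would reflect who was enrolled and not what the CDSS did. The patients such GPs would have recruited would be absent too. The result would then describe GPs able to finish software training, which is narrower than the stated aim of testing promotion of the CDSS in primary care.

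**Working it through.** **1. The plan's own figure.** Sample size gives 12.64% against 28%, ICC 0.02, 90% power, two-sided 0.05 and 30 patients per control centre.
- Pooled two-proportion formula: n = [1.96·√(2·0.2032·0.7968) + 1.2816·√(0.1264·0.8736 + 0.28·0.72)]² / 0.1536² = 143 per arm after rounding up.
- Design effect: 1 + (30 − 1)·0.02 = 1.58. Then 143 × 1.58 = 225.9, so 226 per arm and 452 in total.
- The unpooled version gives 139.0 per arm before clustering and 440 in total.
- The stated 448 lies between the two, and 448/0.9 = 497.8, so 498.

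The sample size reproduces and is not in question here.

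**2. The sections side by side.**
- GP criterion: AF training and CDSS training, both arms (Settings and participants).
- AF training delivered: both arms (Preparation).
- CDSS training delivered: intervention arm only (Preparation).
- Computer-use exclusion and willingness: both arms (Settings and participants).
- Allocation: done and disclosed to administrators; GP enrolment and training: future.

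Only the CDSS-training element differs between what is required and what is delivered. It can be verified in one arm only.

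**3. Strength of the timing inference.** Past tense for allocation and future tense for GP enrolment point to enrolment after allocation. Arm-specific training also needs the arm to be known first. The evidence is not perfect: the Implementation section mixes present and past tense in one sentence.

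**4. Illustration of size (assumptions, not data).** The documents give no GP-level figures.
- Take 12.64% as the average rate with no CDSS effect. If 20% of intervention GPs were screened out and had a 5% rate, the rest would average (12.64 − 0.2 × 5)/0.8 = 14.55%, a shift of +1.9 points. If 30% were screened out with a 0% rate, the rest would average 12.64/0.7 = 18.06%, or +5.4 points.
- The planned difference is 28 − 12.64 = 15.36 points, so these are 12% and 35% of it.
- Chance of a significant result favouring the CDSS when only selection is at work: 448 patients are 224 per arm, or 32 per centre. The design effect is 1 + 31 × 0.02 = 1.62, and the effective n per arm is 224/1.62 = 138.3. A shift of 2, 5 or 8 points over 12.64% gives about 7%, 21% or 43%, against a nominal 2.5% in that direction.

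The higher figures need large one-sided losses of poorly performing GPs, which nothing in the article suggests.

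**The case against.** Several stronger readings are tempting, and the article does not support them.

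- A reader might infer that no control GP can qualify. The criterion speaks of being able to complete the training, which reads most naturally as a capacity at entry. A control GP may have that capacity, although it cannot be checked there.
- A reader might take the clause on not completing the whole study as removing GPs who later abandon the tool. It stands among the entry criteria, for both arms. The patient exclusion in the same section, for those who cannot keep consulting over the coming year, is worded prospectively. Anticipated unavailability is the natural sense, and nothing says that a GP who stops is removed.
- A reader might infer that less computer-able GPs are removed from intervention centres only. The computer-use exclusion applies in both arms, as does willingness, so much of this screening is shared.
- A reader might conclude that the arms do contain different kinds of GP. That is a possibility, not something shown.

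Two safeguards also count. KAP is taken before training, so an imbalance among enrolled GPs would be visible and could be adjusted for. An ITT analysis is planned beside the per-protocol one, though Statistical analysis does not mention GPs separately.

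It can also be said that a condensed article leaves such operating detail to the full protocol. That does not settle the point. The article states both the criterion and the training plan, and the two do not fit. Prescribing has no stated GP-level baseline, so the primary outcome lacks the safeguard that KAP has.

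**Conclusion.** The point holds as a mismatch between eligibility and training that opens an arm-dependent selection step. It rests on two things: the text of Settings and participants against Preparation, which is plain, and GP enrolment after open allocation, which is a well-supported inference. The consequence is a risk of bias in prescribing and patient recruitment, and a smaller one for KAP. Its size cannot be derived from the documents, and the illustrative shifts show only that a modest selection effect would not be harmless. The change is worth making because it is specific and nearly free. It does not call the sample size or the randomisation of centres into question.

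**What to change.** - Remove the reference to CDSS use from the GP inclusion criteria. The same rule (consulting-room role, willingness, ability to complete AF-management training) then applies in both arms.
- Record completion of CDSS training in intervention centres as a measure of uptake, not as a condition of entry.
- Reword the exclusion about completing the whole study as anticipated unavailability, judged at entry in the same way in both arms.
- State that the ITT analysis keeps all enrolled GPs, and the patients of GPs who stop, in the arm of their centre, for KAP and for all patient outcomes.
- Report by arm the numbers of GPs approached, declining and excluded, so that any difference in selection can be seen.

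The cost is two eligibility lines, one analysis sentence and a simple GP log. The one downside is that some intervention GPs may use the tool poorly, so the observed effect may be slightly smaller.

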### Randomization and blinding

#### Sequence generation

Stratified randomization was conducted considering the location of each community health center.

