#### Implementation

The researchers use a computer to generate two random sequences, allocated the eight community health centers in Baoshan District and six CHSs in Jing’an District, respectively, in a ratio of 1:1 into an intervention and a control group to receive CDSS intervention or usual care.

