### Sample size

A previous study reported that 12.64% of patients with AF received appropriate anticoagulants in community health centers of Shanghai [34]. Intracluster correlation coefficient (ICC) was 0.02 [35], the power (1-β) was 90%, and the double-sided significance (α) was 0.05. In the pilot study, the proportion of appropriate anticoagulation increased to 28% in the intervention group, so we expected the proportion to be 28% in this study. Seven community health centers are in each group and we plan to enroll 30 patients from each community health center in the control group, meaning a sample size of 448, or 498 to allow for a 10% loss to follow-up.

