### Statistical analysis

Categorical data will be reported as frequencies and percentages (*n*, %), and a chi-square test will be used to detect any significant differences. Continuous data will be reported as mean ± SD (standard deviation) and compared using a *t*-test if it is on the Gaussian distribution. Otherwise, the data will be reported as the median (IQR (interquartile range)) and compared using the Mann-Whitney *U* test. Linear regression model will be used to compare the continuous data between the distinct groups, considering the interaction of time and allocation. Logistic regression model will be used to detect the effect of the interventions on the primary outcome. Kaplan-Meier (Log-rank test) and Cox proportional hazard models are to be used for the secondary outcomes and safety outcomes. To simplify the analysis, the follow-up time will be recorded as a unit of a month and regardless of start or end. The time will be calculated from this month, if it occurs in the former month; otherwise, it will be calculated from the next month. All outcomes will be evaluated with Mantel-Haenszel statistics and adjusted for the effect of clustering.

Per-protocol (PP) analysis and the intention-to-treat (ITT) analysis will be conducted after filling missing values by multiple imputations. The subgroup analyses will be conducted by whether the CDSS is installed and used in all general clinics or only the AF special consulting room. The sensitivity analyses will be performed by age strata, gender, resident district, and anticoagulants used.

All statistical analyses will be performed with IBM SPSS Statistics, version 26.0 (SPSS Inc) and R (version 4.0.5). A two-tailed *P* < 0.05 will be considered statistically significant.

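### Centres were randomised within two districts, but the primary analysis does not name centre district as an adjustment factor or stratum

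*Protocol article*

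**What the plan says.** Under Sequence generation: "Stratified randomization was conducted considering the location of each community health center". Under Implementation, two sequences "allocated the eight community health centers in Baoshan District and six CHSs in Jing’an District, respectively, in a ratio of 1:1", which gives 4+4 and 3+3 centres. Settings and participants describes one district as suburban and the other as urban.

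Under Statistical analysis, the primary outcome is covered by this sentence: "Logistic regression model will be used to detect the effect of the interventions on the primary outcome". No covariates are listed. The same section applies Mantel-Haenszel statistics, with an adjustment for clustering, to every outcome, but does not say what the strata are. District is mentioned once: "The sensitivity analyses will be performed by age strata, gender, resident district, and anticoagulants used". As worded, that is where the patient lives, not the district of the centre, which was the randomisation stratum.

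**The concern.** Stratified allocation balances the two districts across arms, so a district difference in prescribing does not contribute to the true sampling error of the arm comparison. An analysis without a district term does not know this. It counts the suburban/urban difference as unexplained variation between centres and carries it into the estimated standard error. The result is a test that rejects less often than 5% under the null and has less power than the design can deliver. With only 14 centres, the between-centre component matters, so the stratification could go partly unused.

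**Working it through.** **Inputs.** From Sample size: control proportion ("12.64% of patients with AF received appropriate anticoagulants in community health centers of Shanghai"), intervention proportion 28% ("so we expected the proportion to be 28% in this study"), "Intracluster correlation coefficient (ICC) was 0.02 [35], the power (1-β) was 90%, and the double-sided significance (α) was 0.05", and "Seven community health centers are in each group and we plan to enroll 30 patients from each community health center in the control group". From Implementation: 8 and 6 centres, each 1:1. Not in the documents: the share f of between-centre variance due to district. It is assumed and varied from 0 to 100%.

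**The plan's own figure.** The variance per arm is p(1-p)[1+(m-1)ICC]/(7m).
- Control, m = 30: 0.1264 × 0.8736 × 1.58 / 210 = 0.000831.
- Intervention, m = 34: 0.28 × 0.72 × 1.66 / 238 = 0.001406.
- The sum is 0.002237, so the SE is 0.0473. The difference is 0.28 - 0.1264 = 0.1536, and 0.1536/0.0473 = 3.25. Then 3.25 - 1.96 = 1.29, which is power of 90.1%.
- Total 210 + 238 = 448, and 448/0.9 = 498. The stated size is reproduced. It makes no use of district.

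**Effect of district, by formula.** Take a centre-level analysis with 32 patients per centre (448/14), and write s = p(1-p).
- With district in the model, the variance of a centre proportion is s × [0.02(1-f) + 0.98/32].
- Without it, the residual mean square also absorbs the district sum of squares, on average 14 × 0.02f / 12 (times s).
- f = 50%: 0.0406 with district; 0.0406 + 0.0117 = 0.0523 without. SE ratio √(0.0523/0.0406) = 1.13.
- f = 100%: 0.0306 with district; 0.0306 + 0.0233 = 0.0540 without. SE ratio √(0.0540/0.0306) = 1.33.

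The unadjusted SE is therefore about 13% and 33% too wide. Analytic power is 84.3% without district at f = 0 (12 df). With district (11 df) it is 83.7, 87.2, 90.7, 93.8 and 96.5% for f = 0, 25, 50, 75 and 100%.

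**Simulation.** 8,000 beta-binomial trials per scenario, allocation stratified by district, linear model on the 14 centre proportions, t reference with 12 or 11 df:

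| District share f | Power without → with | Mean SE without → with | Type I error without district |
|---|---|---|---|
| 0% | 83.6 → 83.1% | 0.0464 → 0.0463 | 4.8% |
| 25% | 85.4 → 87.5% | 0.0468 → 0.0440 | 3.8% |
| 50% | 85.6 → 90.5% | 0.0471 → 0.0414 | 2.6% |
| 75% | 86.9 → 93.9% | 0.0477 → 0.0390 | 1.8% |
| 100% | 87.6 → 96.7% | 0.0481 → 0.0363 | 1.2% |

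With district in the model, type I error is about 5% in every row. A repeat simulation gave 2.9% at f = 50% and 1.3% at f = 100%, which is agreement to within simulation error. The gap between 90% and about 84% at f = 0 comes from using a t reference on 12 df rather than the normal approximation, and has nothing to do with district.

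**What the shares mean.** With an 8/6 split, a district difference d adds (8/14)(6/14)d² = 0.245d² to the between-centre variance. The average p(1-p) over the arms is (0.110 + 0.202)/2 = 0.156, so ICC 0.02 corresponds to 0.02 × 0.156 = 0.0031. All of it is used up at d = √(0.0031/0.245) = 0.11, about 11 points. Half is used up at about 8 points.

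**The case against.** **The text does not exclude district.** A reader might infer that no analysis of the primary outcome adjusts for district. The article does not establish that. Mantel-Haenszel statistics are stratified by construction and are applied to all outcomes. The strata cannot be centres, because arm is constant within a centre, so the two districts are a natural candidate. The logistic sentence lists no covariates at all, which is not the same as specifying an unadjusted model, and a covariate list may stand in a fuller document that is not shown. This limits the point but does not remove it: the section does assign roles to other factors, and the only role it gives to district is a sensitivity analysis by patient residence.

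**The loss is conditional.** A reader might also infer that power is certainly lost. No district effect is given. At f = 0 nothing is lost, and adjustment costs about half a point.

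**A large fall in power is not supported.** If a district difference is added on top of ICC 0.02, unadjusted power appears to fall from 84% with no difference to 65% at 15 points. But 15 points adds 0.245 × 0.15² / 0.156 = 0.035 to the ICC, giving about 0.055, which contradicts the plan's input. Within ICC 0.02, unadjusted power does not fall. What is given up is a possible gain.

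**The model named is logistic.** Covariate adjustment does not in general narrow the SE of a log odds ratio, so the centre-level figures do not transfer automatically. District is a centre-level factor, however, and a clustering-adjusted SE contains between-centre variance. In 2,000 simulated trials per scenario with logistic regression and cluster-robust SEs (district differences of 0, 5, 8 and 10 points, added to ICC 0.02), the mean SE went from 0.318 to 0.320, 0.329 to 0.318, 0.353 to 0.321 and 0.377 to 0.327 on adding district. The direction therefore carries over. The sizes do not, because the total ICC in those scenarios exceeds 0.02.

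**Conclusion.** The point holds in a conditional form. The single factor used to stratify the randomisation is not named in the primary analysis, and if centre district is prognostic, leaving it out makes the test conservative. Within the stated ICC of 0.02, naming it is worth about 5 points of power if district explains half of the between-centre variance, and 9 to 10 points if it explains all. Type I error returns to 5% from about 2.6 to 2.9% and 1.2 to 1.3% respectively. If district explains none, adjustment costs about 0.5 to 1 point. These sizes rest on an assumed district share and on a centre-level analysis. Omitting district would not raise the false-positive rate, and the sample size stands. It is a cheap improvement that should be made, not a flaw that threatens the trial's conclusion.

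**What to change.** State that centre district, the randomisation stratum, enters the clustering-adjusted logistic model for the primary outcome as a fixed factor, and name it as the stratum for the Mantel-Haenszel statistics. Do the same in the secondary and safety models where event counts allow. Keep results by district as a subgroup display, and distinguish the centre's district from the patient's resident district.

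The cost is one sentence and one degree of freedom (12 to 11). No new data are needed and 448/498 is unchanged. Because the Blinding section says that data analysts are not blinded, the sentence should be fixed before outcome data are examined.
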